## Abstract

**Introduction:**

Feeding practices developed in early life can impact a child’s nutrition, growth, dental health, cognitive development and lifetime risk of chronic diseases. Substantial evidence suggests ethnic health inequalities, and non-recommended complementary infant feeding practices among UK’s South Asian (SA) population. Nurture Early for Optimal Nutrition aims to use women’s group participatory learning and action (PLA) cycles to optimise infant feeding, care and dental hygiene practices in SA infants <2 years in East London.

**Ethics and dissemination:**

Ethics approval was obtained from University College London (UCL), National Health Service (Health Research Authority (HRA) and Health and Care Research Wales (HRCW)). Results will be published in peer-reviewed journals, presented at scientific conferences/workshops with commissioners, partners and participating communities. Plain language summaries will be disseminated through community groups, websites and social media.

**Trial registration number:**

IRAS-ID-296259 (ISRCTN10234623).

STRENGTHS AND LIMITATIONS OF THIS STUDYThe three-armed approach will allow for comparisons of online and face to face delivery with usual care.The collection and interrogation of process and feasibility data with clearly defined Stop-Go criteria will allow for an informed decision around feasibility of a larger scale evaluation.A broad set of secondary outcome measures will allow for estimation of potential impact, in addition to understanding of the feasibility of capturing reliable and complete data measuring these outcomes.Project capacity precludes the spacing of group sessions according to religious celebrations which might affect retention to group session.Risk of performance and measurement bias as neither participants nor all research staff will be fully blinded.

## Introduction

The first 1000 days of life is important for growth and brain development. There is mounting evidence that influences during pregnancy and infancy may alter lifetime risk of nutrition and dental related diseases.^1^ Feeding practices developed during this period can impact children’s nutrition, growth, dental health, cognitive development, and may lead eventually to heart disease, obesity and diabetes.^2^

Britain’s ethnically diverse population is mostly disadvantaged across a range of socioeconomic outcomes, forming fundamental causes of ethnic health inequalities in the UK.^3^ Some of the widest differences have been observed in the South Asian (SA) population, more so for Pakistani and Bangladeshi communities compared with Indians.^4^

Systematic reviews assessing complementary feeding practices and the sociocultural beliefs underpinning them in children <2 years within SA families in the UK were explored. Despite the adoption of the WHO Infant and Young Children Feeding Guidelines, there remains substantial evidence of non-recommended complementary feeding practices such as early introduction of solids, introduction of minimum dietary diversity or minimum frequency of meals being followed.^5–7^ Contributing factors that persisted postmigration included bicultural issues or low acculturation levels and conflicting information among health professionals, extended family, and religious and community leaders.

Effective early life interventions tailored to different ethnic groups have great potential to reduce the development of short-term and long-term conditions and, thereby, lifetime inequalities. At present, however, few of such interventions exist.^8^ Traditionally, UK health services provide unidirectional information based on guidelines and National Health Service (NHS) recommendations. Specific ethnic groups may be marginalised by this approach as most advice is not tailored to their cultural practices. There is a need for interventions that target these communities through a top-down unidirectional approach and bring a change originating from within the communities. Therefore, it is important to work in partnership with communities thereby building their capacity to work closely with local authorities/stakeholders. The asset-based community development approach has been successful in community development as this helps communities identify their assets through asset mapping and mobilise them to bring along the desired change.^9^

Based on Lakhanpaul and Panchsheeel’s Motivation Awareness Resources Knowledge and Skills model,^10^ current practice lacks the space to understand parents’ motivation and ability to support families in skills development, all of which is key to providing optimal infant feeding, care and dental hygiene support. Considering the resource constraints of the NHS and its 10-Year Forward Plan which aims to shift the emphasis to the community, highlighting a need for interventions that enable communities to use their available community assets. The participatory learning and action (PLA) cycle is an iterative process led by multilingual facilitators through a four-stage cycle of identifying and prioritising contextual issues, designing problem-solving strategies, implementing these strategies and a postimplementation evaluation. The PLA approach is a low-cost, community-based, culturally sensitive intervention that can be adapted from low-income and middle-income countries (LMICs) to high-income countries, as well as to different population groups and topic areas. This strategy is also recommended by the WHO to improve maternal and infant survival.^11^ A meta-analysis of seven cluster randomised controlled trials (RCTs) using PLA in LMICs showed reduced maternal and neonatal mortality by 37% and 23%, respectively.^12^

An RCT and controlled before-and-after study have demonstrated reduced maternal depression, increased exclusive breastfeeding rates and decreased under-5 morbidity.^13^ A Mumbai-based RCT also showed improvements in maternal practices and care-seeking behaviour.^14^ Recognising WHO recommendations and the success of PLA in LMICs, this approach was adopted for the Nurture Early for Optimal Nutrition (NEON) programme.

In NEON phase 1 (intervention development) was codeveloped with the SA community facilitators (CF) (now community researchers (CRs)/independent observers in NEON phase 2), community members, research team and independent experts (ie, health visitors (HVs), dentists, dieticians, nutritionists, general practitioners (GPs) and midwives). This followed the MRC complex intervention framework, which involved using formative research and prior trials as evidence-based factors; microadaptations involved adjusting language, literacy levels for materials, using picture cards, face-to-face and interactive learning delivery methods. This protocol describes NEON phase 2: pilot feasibility cluster RCT.

## Aims and objectives

This pilot feasibility study aims to evaluate the feasibility and inform the design and conduct of a definitive cluster RCT comparing NEON women’s group PLA cycle versus usual care to optimise infant feeding, care and dental hygiene practices in SA infants aged <2 years in East London.

### Primary objectives

Assess: (1) the feasibility of proceeding to a definitive trial against predetermined Go/Stop criteria (ie, recruitment, retention rates, intervention support, acceptability), (2) intervention fidelity and participant’ adherence, (3) implementation of face-to-face versus online intervention arms.

### Secondary objectives

Assess: (1) feasibility, completeness, acceptability and adequacy of blinding when collecting proposed outcomes to establish optimal outcomes and data collection procedures, (2) time needed to competently deliver both versions of NEON intervention, (3) the mean, SD and intervention effect with 95% CI of the proposed primary outcome, child BMI z-score.

## Methods and analysis

### Design

This three-arm pilot feasibility cluster RCT study is expected to run from July 2021 to May 2023 in three East London boroughs. Eighteen clusters defined as borough wards will be randomised with 1:1:1 allocation to two intervention arms (face-to-face or online NEON women’s group PLA cycle) and one control arm (usual care). An online arm enables the trial to continue under COVID-19 restrictions; usual care was selected as control to avoid depriving participants of essential and available infant and maternal care services. Multilingual CFs will deliver interventions in respective ethnic/language groups. Ward-level randomisation is a trade-off between minimising contamination and ensuring maximum SA population representation given the diversity in the ethnic makeup, that is, SA subgroups, of the aforementioned boroughs.

### Patient and public involvement

The research has been codesigned with SA CFs involved in all stages of developing and evaluating the intervention to ensure relevant research questions and an acceptable study design. Development phase, representing different SA communities, is now recruited as CRs to support; protocol development and ethics application by ensuring participants-facing documents are clear, appropriate and sensitively worded; topic guide and questionnaire development; strategy development and troubleshooting (eg, recruitment); interpretation of findings into appropriate and attainable recommendations for practice; review and revision of draft academic papers; dissemination activities and development of plain language summaries.

### Setting

This study will run sequentially in the London Boroughs of Tower Hamlets (TH), Newham (NH) and Waltham Forest (WF), all of which are considered to be among 5% most deprived in England.^15^ The boroughs were analysed in terms of ethnic make-up; in each borough, the six wards with the highest density of Asian population were selected based on census data.^16^ The most common SA ethnic/language groups will be targeted. Figure 1 shows the number of wards and PLA groups by boroughs. Figure 2 shows the overview of participant flow throughout the trial.

**Figure 1 F1:**
[figure not shown]
Overview schematic detailing number of wards and PLA groups by East London boroughs. To illustrate, TH will have two face-to-face Bangladeshi/ Bengali and Sylheti PLA groups (one per ward), two groups of Bangladeshi/ Bengali and Sylheti online PLA group (one per ward) and two Bangladeshi/ Bengali and Sylheti control groups (one per ward). The more the ethnic/ language group in the borough, the more the intervention and control groups. PLA, participatory learning and action.

**Figure 2 F2:**
[figure not shown]
Overview of the NEON pilot feasibility RCT design and participant flow. NEON, Participatory Learning and Action; PLA, participatory learning and action; RCT, randomised controlled trial; SA, South Asian.

### Randomisation

Randomisation of wards will be done before the recruitment by a separate member at University College London (UCL) using the Research Randomizer software for the 18 wards stratified by borough.^17^ The randomised wards will be shared with the RA at the end of recruitment. Once sufficient numbers are recruited in an ethnic/language group, the RA will assign participants to their respective arms. Recruitment will be performed by NHS personnel who will not be aware of the randomisation. CFs/CRs will be made aware of the participant allocation before the PLA sessions start to make contact and invite participants.

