### Allocation concealment and blinding

First, treatment allocation will be concealed from participants and recruiters during participant recruitment to reduce recruitment bias. After recruitment has been completed for that ethnic/language group in the borough, the RA will reveal ward allocation to participants and CFs via text or email, listing postcodes by trial arms to allow CFs to effectively organise and deliver the intervention.

Second, outcome assessors (CRs) will be blinded where possible to reduce measurement bias. This will be achieved by CRs logging the data collected onto an electronic platform that automatically links participant ID to maintain blinding. Baseline measurement of BMI will be done by HVs in each borough who will be blinded.

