### Outcome

#### Primary outcomes

##### Feasibility and process outcome measures

We will collect quantitative and qualitative data to assess Go/Stop criteria (table 1) on recruitment and retention rates, intervention support, acceptability, fidelity and participant adherence using:

Study record: An enrolment log will record all eligible participants, total enrolled, reasons for non-participation, number followed up on child BMI z-score, and the date on how many people responded to adverts/invitations. Prescreen failure logs will record those eligible but not enrolled, with reasons. PLA session audio/video recordings will be collected using secured Dictaphone, video cameras, CCTV and/or Zoom recording.Process measurements: These include Participants’ Feedback Questionnaire, Facilitator’s Feedback Form, PLA Cycle Meeting Register, direct observation of intervention delivery and CF performance by CRs, and Sustainability Assessment Tool (online supplemental material 4).

10.1136/bmjopen-2022-063885.supp4Supplementary data

**Table 1 T1:** Go/Stop criteria for the definitive trial*

Definite Go	Definite Stop
≥50% of eligible participants consenting to pilot feasibility study.	<40% of eligible participants consenting to pilot feasibility trial.
≥80% of mothers attend ≥60% of planned sessions in the intervention arm.	<20% of mothers attend ≥60% of sessions as planned in each intervention arm.
Retention of ≥70% of consented participants for primary outcome data collection.	Retention of <50% of participants at 6 months.
High intervention support with respect to content, frequency, duration and quality.	Low support of intervention procedures.
Intervention is perceived as acceptable.	Intervention perceived as unacceptable.

*The study will have to meet the Definite Go criteria in order for the study to be feasible and to be able to proceed. However, if any one of the Definite Stop criteria is met then the study stops. The ‘Go/Stop’ indicates that it is either feasible or not feasible to proceed to a definitive trial. The progression rules have been approved by the steering and data management team. Should any of the progression rules not be met, assessments and adjustments of the NEON pilot feasibility RCT will be negotiated before proceeding to a definitive trial.

NEON, Nurture Early for Optimal Nutrition; RCT, randomised controlled trial.

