#### Primary individual-level outcome

Child BMI z-score: HVs will measure infants’ length/height, head circumference and weight. The RA will refer to the WHO 2006 growth standard,^2^ using age-adjusted and gender-adjusted length or height(m)/weight (kg)^2^ to provide a comparison on the cluster level.

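### The community researchers named as blinded outcome assessors are told the allocation and observe the sessions, and the sections disagree on who measures follow-up BMI

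*Protocol article*

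**What the plan says.** Under Allocation concealment and blinding, the protocol article states that "outcome assessors (CRs) will be blinded where possible to reduce measurement bias". It gives the means: "This will be achieved by CRs logging the data collected onto an electronic platform that automatically links participant ID to maintain blinding". For disclosure of the arms, the same section says that "the RA will reveal ward allocation to participants and CFs via text or email"; CRs are not on that list.

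The Randomisation section describes the disclosure differently: "CFs/CRs will be made aware of the participant allocation before the PLA sessions start to make contact and invite participants".

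The process measures under Primary outcomes include "direct observation of intervention delivery and CF performance by CRs". Table 2 marks the process outcomes as applying to the intervention groups only.

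The section on data collection and management gives the assessment of post-intervention outcomes to the CRs and the RA. Under Randomisation, the RA is the person who places participants in their arms.

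On BMI, the blinding section says "Baseline measurement of BMI will be done by HVs in each borough who will be blinded", where HVs are health visitors. The definition of the primary individual-level outcome says "HVs will measure infants’ length/height, head circumference and weight" and gives no time point. Table 2 lists the RA and CRs under data collection for BMI z-score at baseline, 14 weeks and 6 months.

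**The concern.** An assessor is blinded only if nothing in the trial's procedures tells that person the arm. Here the same role is declared blinded in one section and informed of the allocation in another. It also has a duty, observing sessions, that exists only in the intervention arms.

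Two things are at stake. First, an outcome that a CR or the RA measures, administers or rates after allocation is open to differential measurement error between arms, and the text tells the reader that this has been guarded against. Second, adequacy of blinding is part of secondary objective 1. A pilot meant to find out whether blinded collection works needs a procedure that could work. As written, the result would mostly reflect the staffing conflict.

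**Working it through.** No arithmetic applies. The check is to set the statements side by side and ask, for each role, whether it knows the arm and whether it assesses outcomes after baseline.

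| Role | Route to knowing the arm | Role in post-baseline outcomes |
|---|---|---|
| CRs | Informed, per Randomisation; not listed as informed, per the blinding section; observe sessions, per process measures | Assess, per Data collection and management and Table 2 |
| RA | Assigns arms (Randomisation) and reveals them (blinding section) | Assesses, per the same two places |
| HVs | None stated; their teams may be invited to one or two sessions | Measure length and weight, with no time point; said to be blinded for baseline only |

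**Step 1: disclosure.** The Randomisation and blinding sections cannot both be right about whether CRs are told. If Randomisation is right, the CRs know the arm before the first session.

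**Step 2: observation.** Suppose the blinding section is right and CRs receive no list. A CR who observes a group still learns that its members are in an intervention arm, because observation takes place only there. Allocation is by ward, so this also shows the arm of that ward's other participants.

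**Step 3: the stated mechanism.** Entering data under a participant ID can hide the arm from someone who sees only the record. It cannot remove knowledge from someone who invited the mother or sat in her group. The mechanism therefore does not deliver what the blinding section claims for it.

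**Step 4: the other assessor.** The alternative to a CR at follow-up is the RA, who holds the allocation. Neither of the two roles given post-intervention assessment is reliably blinded under the text.

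**Step 5: follow-up BMI.** Four places bear on it:
- The blinding section: blinded HVs, baseline only.
- The outcome definition: HVs, no time point, no statement on blinding.
- Table 2: RA and CRs at all three time points.
- Data collection and management: CRs and RA for post-intervention outcomes.

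Table 2 names the RA and CRs even at baseline, where the blinding section says HVs measure. Its column therefore need not identify the person taking the measurement. The four places leave the follow-up measurer undetermined.

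**Step 6: which outcomes are exposed.** Exposed outcomes are those a CR or the RA measures, administers or rates after allocation. These include BMI if either takes the measurement, and the audio/video recordings that Table 2 gives to the RA alone. Parental feeding style and the food diary are self-reported by mothers who know their arm, so blinding the assessor would change little. Child development, GP use and dental caries come from routine records.

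**The case against.** The best defence is disclosure. Blinding is promised only as far as it can be achieved, and the listed limitations concede a risk of measurement bias because not all research staff will be blinded. That is fair, and it means the authors do not claim complete blinding. But the limitation does not say that the named assessors are the unblinded staff, and the blinding section still puts forward a mechanism that cannot work for them.

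A second defence is that different CRs might observe and assess. This would help, but no such separation is stated, and the Randomisation section informs CRs without distinction. The blinded statistician described under Analysis does not answer the point, because measurement bias arises before analysis.

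A reader might infer three stronger things that the document does not support:
- *Follow-up BMI is unblinded.* The outcome definition has HVs measuring without limit of time, and Table 2 does not identify the measurer. What is shown is inconsistency.
- *The HVs are unblinded because they attend sessions.* Their teams may be invited at participants' request, but nothing says that those who attend are those who measure.
- *The decision to progress is compromised.* The criteria in Table 1 concern consent, attendance, retention, support and acceptability. None uses a BMI value. The BMI effect is a secondary objective, and its estimation is conditional on low recruitment bias and adequate adherence to the protocol.

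**Conclusion.** The point holds in this form: the blinding claimed for the CRs does not hold as written, and the article is inconsistent on who measures BMI at 14 weeks and 6 months and whether they are blinded. The first part follows from the text alone. It would fall only if an unstated separation of CR duties exists and the Randomisation wording on CRs is a slip.

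No size can be put on the resulting bias. That would need an assumed misreading that differs by arm, and the document offers nothing on which to base one. The consequence is confined to assessor-collected outcomes and to secondary objective 1. This is a pilot whose progression rules do not use the BMI value, so it should be fixed but is not critical.

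**What to change.** 1. In Randomisation, remove CRs from those told the allocation, so that CFs or the RA invite participants. This brings it into line with the blinding section.
2. Reconcile the blinding section, Table 2, the outcome definition, and Data collection and management. State that length and weight at 14 weeks and 6 months are taken by HVs who are not told the allocation and do not attend that ward's sessions.
3. Separate CRs who observe sessions from CRs who assess outcomes, by ward or group within the existing team. Separation by borough would not work for every language: the Sample size section places the Bengali/Sylheti group only in Tower Hamlets and the Gujarati group only in Newham.
4. Where language matching makes separation impossible, declare those outcomes unblinded and drop the claim that ID logging maintains blinding. The RA holds the allocation, so outcomes that only the RA collects after allocation should be described in the same way.
5. Record each assessor's guess of arm, so that secondary objective 1 has data behind it.

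The cost is rewording, one extra item on the collection form, and a scheduling constraint on CRs and HVs. The document does not describe HV capacity for the 14-week and 6-month measurements, so this should be confirmed with the study partners.

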### Eligibility criteria

#### Participants

Inclusion

Mothers or female carers of an infant <24 months.Indian, Pakistani, Sri Lankan or Bangladeshi background.Resident in a randomised study ward in TH, NH and WF.Willing and able to provide informed consent.

Exclusion

<18 years old.Anticipating moving out of a priori defined geographical areas before or after delivery.Current or recent participation in another study within 4 weeks of trial commencement.

